### CREDI tool

Child development will be assessed using the Caregiver Reported Early Development Index (CREDI) – Short Form, a caregiver-reported instrument designed for children from birth to 36 months. Trained study staff will guide caregivers through the structured questions, and the CREDI Short Form responses will be scored using the official CREDI scoring algorithms and reference parameters to generate age-standardised developmental status scores. The tool captures developmental milestones across key domains including motor, language, cognitive and socio-emotional development and yields a summary score reflecting overall developmental status. The tool has been validated for population-level measurement in diverse cultural settings and has demonstrated good internal consistency and concurrent validity with more intensive clinician-administered instruments such as the Bayley Scales of Infant and Toddler Development.
^
18
^

In this study, developmental outcomes will be analysed as continuous summary scores and compared across exposure groups using longitudinal regression methods. The study prioritises comparability and feasibility over clinical diagnosis, and findings related to child development will therefore be interpreted as indicators of group-level developmental patterns rather than diagnostic outcomes for individual infants. The use of CREDI allows for standardized developmental assessment across visits and study groups, while remaining practical and culturally appropriate for use in routine clinical and implementation research settings.
^
19
^

### Missed visits

All dosing visits for injectable and oral PrEP are aligned with those of the parent PathToScale and LINK implementation studies. As the CABMILK study is leveraging the platform of the implementation of PathToScale and LINK studies, missed dosing or follow-up visits are inevitable. Nevertheless, any such missed dosing or follow-up visits, including sample collection visits, will be conducted as soon as it is possible to do so. This will be documented appropriately in the participant’s file.

Retention and evaluable pairs: The primary pharmacokinetic analysis will be conducted on mother–infant pairs who contribute matched maternal plasma, breastmilk, and at least one infant dried blood spot sample within the month-7 window. Losses before the month-7 sampling visit, missed CAB-LA doses, and out-of-window sampling will be documented and reported as implementation outcomes. Baseline characteristics of mothers who do and do not reach the evaluable PK sampling visit will be compared descriptively. Retention is supported through appointment reminders, alignment of CABMILK visits with routine postnatal and under-five clinic contacts, travel reimbursement, and, where acceptable to the mother, a home visit to complete a missed sampling occasion. Recruitment will continue until the target of 25 evaluable pairs in the CAB-LA group has been met bearing in mind study timelines.

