**Methods:**

CABMILK is an observational pharmacokinetic study nested within two ongoing CAB-LA implementation studies in Malawi. A total of 100 mother–infant pairs will be enrolled: 25 receiving CAB-LA, 25 receiving oral PrEP, and 50 PrEP-naïve. Serial maternal plasma and breast milk samples will be collected to quantify cabotegravir concentrations using validated LC–MS/MS assays and to estimate milk-to-plasma ratios and infant exposure. Infant safety monitoring will include clinical assessments, growth measurements, and developmental evaluation using the Caregiver Reported Early Development Index (CREDI) Short Form over 8 months of follow-up.

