### Step 1-
CABMILK study- Cabotegravir maternal, breastmilk and infant pharmacokinetic study

We hypothesise that cabotegravir administered as long-acting PrEP in lactating mothers may be detectable in breast milk and infant plasma, but that the magnitude of infant exposure and its clinical significance remain uncertain. The study is designed to quantify breast milk transfer, estimate infant systemic exposure, and evaluate infant safety. If infant exposure occurs at very low, subtherapeutic concentrations, this could have theoretical implications for resistance in the event of HIV acquisition during breastfeeding; however, it is also possible that transfer is minimal and clinically reassuring and safe. CAB would transfer.

*Cabotegravir pharmacokinetic sampling: maternal plasma, breastmilk, and infant plasma*

25 lactating mothers initiating CAB PrEP within the PathToScale Study or LINK Study will be approached for participation in the study. Since CAB has a half-life of 40 days
^
9,
14
^ it would be expected to attain a steady state in the mother at least after 4 half-lives
^
16
^ (i.e. in the case of CAB, at least 160 days) from the first initial dose. To ensure that we conduct pharmacokinetic sampling of CAB at steady state, we will collect samples for CAB concentrations before the 5th CAB maternal dose (i.e. before the maternal dose at 7 months postpartum).

In mothers, 5 mL of venous blood will be collected using calibrated EDTA tubes. It will be separated in the laboratory to collect plasma and frozen in at least two aliquots at -80 degrees Celsius in readiness for a validated liquid chromatography–tandem mass spectrometry (LC–MS/MS) assay. Breastmilk CAB samples will be paired and collected by manual expression at pre-dose and at the expected time of maternal peak (Cmax), 7 days (±3) post-5th CAB dose. No more than 5 mL of breast milk will be collected in a clear container at each sampling time point. Thereafter, the sample will be frozen in at least two aliquots and stored at -80 degrees Celsius in readiness for cabotegravir assay. Therefore, each mother will contribute two breastmilk and blood samples.

To characterise and profile infant CAB exposure from breastmilk, 200 μL of infant capillary blood will be collected through a finger/heel prick at the expected time of trough- (sample collected before dosing in the mother) and peak (expected Cmax) concentrations at 7 days (±3)
^
17

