### Step 2-
Cabotegravir safety, growth pattern and development study

We hypothesise that there will be no difference in the incidence of adverse events or illnesses, growth, and development between infants exposed to breast milk CAB and those exposed to breast milk oral PrEP. 25 mother-infant pairs from Step 1 (mothers receiving CAB for PrEP), 25 other mother-infant pairs from the oral PrEP group of the PathToScale and LINK studies and 50 mother-infant pairs naïve of PrEP, matched to those in the CAB PrEP group, will be followed up for eight months from the time of maternal PrEP initiation in the PrEP groups or a similar time in the PrEP naïve group. The PathToScale and LINK studies are following up mothers in the CAB group from the initiation visit, 1 month later and, thereafter, every 2 months. In our study we will follow a similar schedule for all three groups with a final exit visit scheduled at eight months post initial CAB dose. This will result in 10 scheduled visits in the CAB group and six in the oral PrEP and no PrEP groups. The CAB LA PrEP group will have four additional visits for PK sampling at month 7. In the present CABMILK Study, we will utilise all six planned visits to assess the incidence of reported adverse events and infant growth by measuring anthropometric indices (weight-for-height and height-for-age) as well as head circumference-for-age. The same visit schedule and safety assessments will be applied to the oral PrEP and PrEP-naïve groups. Infant growth and neurodevelopment will be longitudinally assessed at all six study visits using the Caregiver Reported Early Development Instrument (CREDI).

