### Sample size determination and power calculation

Sample size calculation has been primarily based on step 1 of the CABMILK study. Step 2 leverages on the previous step. In Step 1 (Cabotegravir maternal, breastmilk and infant pharmacokinetic study), previous data on 600 mg intramuscular CAB in adults yielded an area under the concentration-time curve (AUC0-∞, μg*h/mL, [range]) of 4172 [2839–6597] with a coefficient of variation of 24%.
^17^ Assuming a similar coefficient of variation, the inclusion of 25 breastfeeding infants will provide >95% precision to estimate overall infant CAB exposure.

Step 2 (Prospective observational cohort follow-up of mother–infant pairs): Detecting rare safety outcomes or subtle neurodevelopmental effects related to cabotegravir exposure would require substantially larger and longer-term studies. Accordingly, Step 2 is designed as a prospective observational cohort to describe infant exposure and characterise safety signals rather than to support formal inferential comparisons. Safety outcomes will include reported adverse events, growth patterns, and changes in developmental status over time.

We plan to enrol 100 mother–infant pairs (25 CAB-LA, 25 oral TDF/FTC PrEP, and 50 PrEP-naïve). This sample size is intended to provide a reasonable descriptive profile of safety and developmental outcomes across exposure groups. The larger PrEP-naïve group will support more stable estimation of background patterns against which findings in the exposed groups can be contextualised.

Child development will be assessed using the CREDI Short Form, a caregiver-reported tool that provides a summary developmental status score suitable for population-level description rather than clinical diagnosis. Assessments over 8 months of follow-up will allow characterisation of short-term developmental trajectories, while recognising that longer-term outcomes cannot be determined within this study.

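### Twenty-five CAB-LA pairs is an enrolment figure in one place and an evaluable target in another; the Step 2 safety set is left open, and the primary PK set excludes samples the planned model could use

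*Protocol article*

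**What the plan says.** **Enrolment.** The Abstract (Methods) states: "A total of 100 mother–infant pairs will be enrolled: 25 receiving CAB-LA, 25 receiving oral PrEP, and 50 PrEP-naïve". The sample size section repeats the same split, and the section on study place and setting gives a total of n=100. The Step 1 text uses a third term: "25 lactating mothers initiating CAB PrEP within the PathToScale Study or LINK Study will be approached for participation in the study".

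**Evaluability.** The Missed visits section (retention paragraph) sets a different target: "Recruitment will continue until the target of 25 evaluable pairs in the CAB-LA group has been met bearing in mind study timelines". The primary pharmacokinetic analysis is confined to pairs "who contribute matched maternal plasma, breastmilk, and at least one infant dried blood spot sample within the month-7 window". The same section accepts that missed dosing and follow-up visits cannot be avoided and has missed sampling visits carried out as soon as possible. Losses before month 7 and out-of-window samples are reported as implementation outcomes. It also compares the baseline characteristics of mothers who do and do not reach evaluable sampling.

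**Safety group.** Step 2 describes the CAB-LA group as "25 mother-infant pairs from Step 1 (mothers receiving CAB for PrEP", to be followed for eight months from PrEP initiation. The PrEP-naïve pairs are matched to this group.

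**PK method.** Table 2 plans non-linear mixed-effects modelling across maternal plasma, milk and infant plasma.

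**The concern.** Enrolling 25 pairs and recruiting until 25 are evaluable are different stopping rules. A protocol that expects missed visits cannot satisfy both and keep a total of 100. No loss allowance and no enrolment ceiling appear.

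The ambiguity carries into Step 2. Once more than 25 CAB-LA pairs are enrolled, a safety group of 25 from Step 1 cannot be all of them, and the evaluable pairs are the only subset of 25 the protocol describes. If that subset were used, the CAB-LA group alone would be conditioned on reaching month-7 sampling. Infants whose mothers stopped or whose pairs were lost would drop out of the safety description, and the CAB-LA group could look safer than it was. The group to which PrEP-naïve pairs are matched would be unclear as well.

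The PK set is a separate matter. Requiring plasma, milk and an in-window infant spot from the same pair sets aside data that are still collected and that carry information on the primary quantities.

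**Working it through.** **1. The plan's own precision figure.** Inputs from the sample size section: CV = 24% (adult AUC, assumed similar in infants), n = 25. Reading precision as 1 − relative standard error, with RSE = CV/√n:

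- n = 25: 0.24/√25 = 0.0480, precision 95.2%. This reproduces the stated figure of more than 95%.
- n = 24: 0.24/√24 = 0.0490, precision 95.1%.
- n = 23: 0.24/√23 = 0.05004, precision just under 95.0%.

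The claim therefore needs at least 24 infants in the analysis. Reading it as a 95% confidence interval half-width does not reproduce it: at n = 25 the half-width is 9.4% (normal) or 9.9% (t, 24 df), and a half-width below 5% would need 89 or 91 infants.

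**2. What each reading of 25 implies.** The protocol states no loss rate, so the rates below are assumptions. If 25 is the evaluable target, CAB-LA enrolment = 25/(1 − d), rounded up, and the total adds 25 + 50 = 75. If 25 is enrolment, evaluable pairs = 25(1 − d), rounded down.

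| Assumed loss d | CAB-LA enrolled for 25 evaluable | Total | Evaluable if 25 enrolled | 1 − RSE | 95% half-width (t) |
|---|---|---|---|---|---|
| 10% | 28 | 103 | 22 | 94.9% | 10.6% |
| 15% | 30 | 105 | 21 | 94.8% | 10.9% |
| 20% | 32 | 107 | 20 | 94.6% | 11.2% |
| 25% | 34 | 109 | 18 | 94.3% | 11.9% |
| 30% | 36 | 111 | 17 | 94.2% | 12.3% |

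Only d = 0 lets 25 enrolled, 25 evaluable and a total of 100 all hold.

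**3. What a restricted safety group would do.** This is an illustration on assumed rates, not a prediction. At 20% loss, 32 pairs are enrolled and 7 are not evaluable. Suppose 20% of the 25 evaluable infants have an adverse event.

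- If 40% of the other 7 do: (25 × 0.20 + 7 × 0.40)/32 = 7.8/32 = 24.4% among all enrolled, against 20.0% in the evaluable group.
- If 60% of the other 7 do: (5 + 4.2)/32 = 28.75%.
- If the rates are equal, there is no bias.

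**4. Which PK data the primary rule excludes.** Table 1 places every PK sample at visits 5 to 9, from the month-7 pre-dose visit onward. Pairs lost before then have no PK samples to exclude. The rule affects pairs with incomplete or out-of-window sets. For example, a plasma–milk pair without an in-window infant spot still informs the milk-to-plasma ratio, and a mixed-effects model can use a late sample at its actual time since dose. The window is also not fixed consistently: day 14 carries ±3 days in Table 1 and ±4 in the Step 1 text. These need to be reconciled because window status helps decide who enters the primary set.

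**The case against.** A reader might infer that replacing dropouts produces a survivor-selected safety group. The protocol does not say so. The evaluable rule is written for the primary pharmacokinetic analysis only. Step 2 describes its CAB-LA group by receipt of CAB and follows pairs from PrEP initiation. Table 1 schedules adverse event assessment at every scheduled CAB-LA visit from month 0, and the Data analysis section plans incidence rates and Kaplan–Meier curves, which accommodate partial follow-up. All of this points towards including everyone. What stands is that the set is undefined once more than 25 pairs are enrolled, and the one stated check compares mothers' baseline characteristics, not infant outcomes.

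A reader might also infer that replacement discards PK data. It does not, because pairs lost before month 7 have none. The complete-set rule is also fairly mild: one of five infant spots is enough, make-up and home visits are offered, and secondary use of other samples is not ruled out. Further analysis sets may well be in the unseen analysis plan. Even so, the protocol itself fixes the restricted set as primary, so that choice is open to comment.

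The numerical effects are modest. On the plan's own metric, precision falls only from 95.2% to 94.2% at 17 infants. The exact 95% interval for 5 events in 25 infants is about 7% to 41%, far wider than the illustrated bias, and the safety analyses are already labelled descriptive. The recruitment rule is qualified by study timelines and could be read as the specific rule that overrides the planned total. That reading is sensible, but the text should say it.

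**Conclusion.** The inconsistency is real and should be corrected. Twenty-five cannot be both the number enrolled and the number evaluable unless loss is zero, and the protocol's only precision statement depends on the evaluable reading (at least 24 infants). At an assumed 10–30% loss the true enrolment is 28–36 CAB-LA pairs and 103–111 in total; these figures are only as good as that assumption.

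The safety concern is conditional. If Step 2 were limited to the evaluable pairs, selection would act on the CAB-LA group alone and could flatter it, but nothing in the protocol imposes that limit. The PK concern is likewise limited to incomplete or out-of-window sets. How many there will be is unknown, so no size can be given for the information lost. Enrolment is already under way, so the definitions are best settled before results are seen.

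**What to change.** 1. State that 25 is the evaluable CAB-LA target. Restate CAB-LA and total enrolment as a range with the assumed loss beside it (28–36 and 103–111 at 10–30%), with a ceiling, and align the Abstract, the setting section, Step 1 and the sample size section.
2. State that the Step 2 CAB-LA group is every enrolled pair whose mother received at least one CAB-LA injection, whatever its PK evaluability, using all follow-up obtained to month 8. Say that this is the group to which PrEP-naïve pairs are matched.
3. Fit the primary PK model to all available samples at actual times since dose. Keep the complete, in-window set as a sensitivity analysis, and reconcile the two day-14 windows.

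The cost is mainly wording, a higher stated total that matches the recruitment rule already in force, and slightly more analysis work.

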### Sample size determination and power calculation

Sample size calculation has been primarily based on step 1 of the CABMILK study. Step 2 leverages on the previous step. In Step 1 (Cabotegravir maternal, breastmilk and infant pharmacokinetic study), previous data on 600 mg intramuscular CAB in adults yielded an area under the concentration-time curve (AUC0-∞, μg*h/mL, [range]) of 4172 [2839–6597] with a coefficient of variation of 24%.
^17^ Assuming a similar coefficient of variation, the inclusion of 25 breastfeeding infants will provide >95% precision to estimate overall infant CAB exposure.

Step 2 (Prospective observational cohort follow-up of mother–infant pairs): Detecting rare safety outcomes or subtle neurodevelopmental effects related to cabotegravir exposure would require substantially larger and longer-term studies. Accordingly, Step 2 is designed as a prospective observational cohort to describe infant exposure and characterise safety signals rather than to support formal inferential comparisons. Safety outcomes will include reported adverse events, growth patterns, and changes in developmental status over time.

We plan to enrol 100 mother–infant pairs (25 CAB-LA, 25 oral TDF/FTC PrEP, and 50 PrEP-naïve). This sample size is intended to provide a reasonable descriptive profile of safety and developmental outcomes across exposure groups. The larger PrEP-naïve group will support more stable estimation of background patterns against which findings in the exposed groups can be contextualised.

Child development will be assessed using the CREDI Short Form, a caregiver-reported tool that provides a summary developmental status score suitable for population-level description rather than clinical diagnosis. Assessments over 8 months of follow-up will allow characterisation of short-term developmental trajectories, while recognising that longer-term outcomes cannot be determined within this study.

Comparative analyses will be exploratory. Longitudinal growth indices will be analysed using linear mixed-effects models (or generalized estimating equations) to account for repeated measures, and developmental status (continuous CREDI summary score) will be compared across groups using adjusted regression models. Because exposure groups are not randomised, analyses will be interpreted as observational associations and adjusted for prespecified maternal and infant confounders. Results will emphasise effect sizes and confidence intervals. We acknowledge that the study is not powered to detect subtle differences, rare events, or long-term neurodevelopmental outcomes, and findings will therefore be interpreted cautiously and used to inform the design of future larger studies.

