Breast milk and blood samples will be shipped to the University of Cape Town’s Division of Clinical Pharmacology Laboratory or the Infectious Diseases Institute Laboratory in Uganda for quantification of cabotegravir concentrations. Samples will be analysed using a validated liquid chromatography–tandem mass spectrometry (LC–MS/MS) assay capable of detecting very low concentrations of cabotegravir in plasma, breast milk, and dried blood spot matrices. The assay has been validated in accordance with international bioanalytical method validation guidelines, including assessment of accuracy, precision, recovery, matrix effects, and analyte stability. The lower limit of quantification (LLOQ) is expected to be in the low ng/mL range, sufficient to detect concentrations anticipated in infant samples. External quality control samples and calibration standards will be included in each analytical run.

Shipment of samples outside Malawi is required because this highly sensitive LC–MS/MS method for cabotegravir is not currently available locally.

*Information on other factors that could impact CAB breastmilk exposure*

Two classes of variable are recognised as potentially affecting cabotegravir concentrations in breastmilk and the resulting infant exposure: (a) infant feeding pattern, and (b) maternal nutritional status. Infant feeding will be captured at every visit using standard feeding indicators (exclusive vs mixed) and the timing and frequency of feeds relative to sampling and will be entered into pharmacokinetic and safety analyses as a time-varying covariate. Maternal pre-injection weight will be measured at baseline and at each dosing visit and evaluated as covariates on cabotegravir apparent clearance and on the milk-to-plasma ratio in the population PK model. We acknowledge as a limitation that the study does not directly measure milk fat fraction or detailed maternal dietary intake, and therefore cannot fully resolve any indirect effect of maternal diet on infant cabotegravir exposure.

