To profile the extent of CAB transfer in breast milk and determine its pharmacokinetics in infants whose mothers receive long-acting injectable cabotegravir for HIV preexposure prophylaxis (PrEP).	We will use non-linear mixed effects models to determine the compartmental pharmacokinetics of CAB from maternal plasma to breast milk to infant plasma. We will first calculate the milk: plasma ratio to determine the average milk CAB concentration compared with the average maternal plasma concentration. Second, we will utilise individual predicted infant CAB concentrations to calculate infant overall exposure (AUC0-∞) and estimate CAB infant half-life as well as elimination rate constant. Third, we will estimate the CAB dose ingested by each infant, through breast milk, relative to the maternal dose; the relative infant dose (RID). ^ 25 ^ This RID will allow us to determine the extent of CAB breast milk exposure that would result in attained concentrations in the infant’s blood that are above or below the protein-adjusted IC90 of 0.166 μg/mL. ^ 26 ^	CAB transfer to the infant through breast milk, and profile the attained infant concentrations.
To determine the association of breast milk CAB exposure and infant safety outcomes (growth pattern, neuro-cognitive development, and incidence of adverse events).	Firstly, mean anthropometric indices (weight-for-height, height-for-age, head circumference-for-age) will be compared across three groups using independent t-tests. Secondly, adverse events (overall morbidity) by the end of follow-up will be compared across the three groups using Chi-squared tests. Age-standardised CREDI summary scores (z-scores) analysed as continuous outcomes, reported as adjusted mean differences with 95% confidence intervalsUsing linear regression, we will assess whether breast milk CAB concentrations predict growth patterns and morbidity, adjusting for infant age, sex socio-economic status, birth weight and gestation age at birth. Random effects models will account for intra- and interindividual variability in repeated measurements. Exploring this analysis may inform algorithms for monitoring CAB safety signals in infants. These algorithms could be validated in larger studies and incorporated into routine practice for early detection of CAB-related risks in infants.	Impact of CAB breast milk exposure on infant growth and neurocognitive development in comparison to the standard daily oral PrEP.

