## Limitations

This study has several limitations. Enrolment from birth to five months spans a period of rapid ontogeny of Uridine Diphosphate Glucuronosyltransferase 1A1 (UGT1A1)-mediated glucuronidation and developmental change. Although population pharmacokinetic modelling incorporating maturation functions and age-standardised growth and developmental outcomes will be used, the small number of infants within age strata limits precision in characterising exposure–age relationships; findings at younger ages should therefore be interpreted with caution. Secondly, the study is not powered to detect between-group differences in infant safety, growth, or developmental outcomes, and these analyses are consequently descriptive and hypothesis-generating, with formal inference deferred to larger studies. Thirdly, infant feeding patterns and maternal nutritional status may influence infant exposure; feeding will be captured longitudinally and incorporated as a time-varying covariate, while maternal weight will be evaluated in relation to cabotegravir clearance and milk-to-plasma ratios. However, the study does not directly measure milk composition or detailed maternal dietary intake, limiting the ability to fully assess indirect dietary effects. Finally, as exposure groups are self-selected, comparative analyses are observational and exploratory, and although adjusted and sensitivity analyses will be undertaken where feasible, residual confounding cannot be excluded.

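### The precision claimed for infant exposure is undefined and rests on an adult CV; at that CV the 95% confidence interval is about ±10%, and the infant CV is unknown

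*Protocol article*

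**What the plan says.** Under the heading on sample size determination and power calculation, the protocol article bases its sample size primarily on Step 1, the pharmacokinetic step. The input is external: "previous data on 600 mg intramuscular CAB in adults yielded an area under the concentration-time curve" "of 4172 [2839–6597] with a coefficient of variation of 24" per cent. The conclusion follows directly: "Assuming a similar coefficient of variation, the inclusion of 25 breastfeeding infants will provide >95% precision to estimate overall infant CAB exposure".

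No confidence level, interval width or target is attached to the word precision, and no reason is given for expecting infants to vary as those adults did. Step 2 is described as resting on Step 1 and as descriptive, so this sentence is the only quantitative justification of sample size in the document.

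Three other places bear on it:

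- Table 2 (Data analysis) defines the quantity to be estimated: "we will utilise individual predicted infant CAB concentrations to calculate infant overall exposure (AUC0"-∞).
- The Step 1 text on other factors says: "Two classes of variable are recognised as potentially affecting cabotegravir concentrations in breastmilk and the resulting infant exposure". It names infant feeding pattern and maternal nutritional status, and feeding is recorded as exclusive or mixed.
- The Data analysis section puts a maturation function on apparent clearance, and the Limitations section says the enrolment age range "spans a period of rapid ontogeny of Uridine Diphosphate Glucuronosyltransferase 1A1 (UGT1A1)-mediated glucuronidation".

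**The concern.** There are two separate difficulties.

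First, a precision above 95% sounds like a statement about a confidence interval, or about being within 5% of the truth. The figure that reproduces it is a standard error subtracted from one, which is neither. A standard error of 4.8% corresponds to a 95% confidence interval roughly twice as wide on each side.

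Second, the CV describes a different quantity. It measures how much exposure differs between adults who received the injection. Exposure of a breastfed infant depends on the mother's exposure and then on transfer into milk, the amount of milk taken and the infant's own clearance. If these vary roughly independently of maternal exposure, they add to the variability. The protocol itself plans to collect or model several of them.

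At stake is what ethics reviewers and readers are told the primary objective will deliver. No test, decision rule or endpoint definition depends on the figure.

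**Working it through.** **Inputs from the protocol article.** CV = 24% (adult AUC0-∞) and n = 25 infants (sample size section). 25 is also the target number of evaluable pairs (Missed visits section). No confidence level is stated, so a two-sided 95% interval is assumed. No infant or milk CV is given.

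**1. Reproducing the stated figure.** Relative standard error = CV/√n = 0.24/√25 = 0.048. One minus this is 0.952, just over 95%. This reading needs no target that the document does not state.

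**2. The 95% confidence interval at the same CV.**

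- Arithmetic scale, t with 24 degrees of freedom: 2.064 × 0.048 = 0.099, or ±9.9%. With the normal quantile: 1.960 × 0.048 = 0.094, or ±9.4%.
- Log scale: σ = √ln(1 + 0.24²) = 0.237. The factor is exp(2.064 × 0.237/5) = 1.103, with reciprocal 0.907. The interval for the geometric mean is −9% to +10%.
- A half-width of 5% at this CV would need about 91 infants (t) or 89 (normal).

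The log scale suits these data. The quoted adult range is right-skewed: it runs 4172 − 2839 = 1333 below the central value and 6597 − 4172 = 2425 above it.

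**3. How far the claim stretches on its own metric.** One minus the standard error is at least 95% only if CV/5 ≤ 0.05, that is, CV ≤ 25%. At a CV of 30% it is 94%, at 50% it is 90%, and at 100% it is 80%. At a CV of 24% it also fails with 23 evaluable pairs: 0.24/√23 = 5.004%. The Missed visits section qualifies the target: "Recruitment will continue until the target of 25 evaluable pairs in the CAB-LA group has been met bearing in mind study timelines".

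**4. Infant exposure over assumed CVs.** The CVs below 24% in the table are assumptions, not figures from the document. With n = 25, σ = √ln(1 + CV²) and the factor is exp(2.064σ/5).

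| Infant CV | σ | Factor | 95% CI for geometric mean |
|---|---|---|---|
| 24% (equal to adult) | 0.237 | 1.103 | −9% to +10% |
| 40% (assumed) | 0.385 | 1.172 | −15% to +17% |
| 60% (assumed) | 0.555 | 1.257 | −20% to +26% |
| 100% (assumed) | 0.833 | 1.410 | −29% to +41% |

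These intervals treat each infant's AUC as known. In the study it will be predicted from a model, and a pair counts as evaluable with as few as one infant blood spot, so estimation error is not included.

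**The case against.** The strongest reply is that nothing has been miscalculated. The figure reproduces, Step 1 is an estimation exercise, and the study is open about its limits: the Step 1 hypothesis calls the magnitude of infant exposure uncertain, and the Limitations section concedes limited precision for exposure–age relationships. That stands as far as it goes. However, neither place corrects the overall claim, and a reproducible figure can still be badly labelled.

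The standard-error reading is also an inference. Another route passes 95%: at a CV of 24% the probability that the sample mean lies within ±10% of the true mean is 2Φ(0.10/0.048) − 1 = 96.3%. The document states no ±10% target, so this fits less well, but it cannot be excluded. Either way the 95% confidence interval is about ±10%, and the term needs defining.

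Three stronger conclusions are tempting and are not supported:

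- *That the protocol promises infant exposure to within 5%.* A reader might infer this, and it would be wrong: the probability of the mean lying within ±5% is about 70% at a CV of 24%. But the document gives no half-width, so it makes no such promise in terms.
- *That the infant interval will be far wider.* Only the direction is supported, and only if the added sources of variation do not offset maternal variation. No infant CV is given. The maturation argument is also weaker than it first appears: the ontogeny remark concerns age at enrolment (birth to under five months), whereas sampling is at month 7 after enrolment, at roughly 7 to 12 months of age. Feeding pattern is the firmer ground.
- *That 25 pairs are too few.* On the arithmetic scale the 95% half-width stays within ±20% up to a CV of about 48% (0.20 × 5/2.064 = 0.48), and the protocol sets no precision requirement that would be missed.

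**Conclusion.** The point holds as a defect of statement and of input, not of arithmetic or of design. The claimed precision is undefined. On its best-fitting reading it is one minus a 4.8% relative standard error, while the 95% confidence interval at the same CV is about ±10%. The adult CV is applied to infants without justification, and the protocol's own account of feeding pattern and clearance maturation makes a larger infant CV likely, by an unknown amount.

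The ±10% result assumes a two-sided 95% interval, 25 evaluable pairs and a between-subject CV of 24%. The wider intervals rest on assumed CVs and approximate log-normality, and they show sensitivity rather than forecast the result. This should be fixed, because it is the sole quantitative support for the sample size. It gives no ground for changing n.

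**What to change.** Delete the phrase claiming more than 95% precision, keep n = 25, and replace the sentence with wording such as:

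*With 25 evaluable pairs, the 95% confidence interval for geometric mean infant exposure is about −9% to +10% if the infant CV equals the adult value of 24%. The infant CV is unknown; at assumed CVs of 40%, 60% and 100% the interval is about −15% to +17%, −20% to +26% and −29% to +41%.*

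If the investigators have data that support a narrower range of infant CVs, they should cite them and use that range. The text should not transfer the ±10% to maternal exposure in this study either: the 24% is for AUC0-∞ in earlier adult data, whereas each mother here gives two plasma samples.

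The cost is one sentence and a less favourable stated precision. No participants, visits or analyses are added.
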